# Does pragmatically structured outpatient dietary counselling reduce sodium intake in hypertensive patients? Study protocol for a randomized controlled trial

**DOI:** 10.1186/s13063-015-0794-y

**Published:** 2015-06-17

**Keywords:** Hypertension, Blood pressure, Salt, Sodium, Dietary modification, Dietary counselling, Lifestyle modification, Clinical trial

## Abstract

**Background:**

Hypertension is highly prevalent among adults, and is the most important modifiable risk factor for cardiovascular events, in particular stroke. Decreasing sodium intake has the potential to prevent or delay the development of hypertension and improve blood pressure control, independently of blood pressure lowering drugs, among hypertensive patients. Despite guidelines recommending a low sodium diet, especially for hypertensive individuals, sodium intake remains higher than recommended. A recent systematic review indicated that the efficacious counselling methods described in published trials are not suitable for hypertension management by primary care providers in Canada in the present form. The primary reason for the lack of feasibility is that interventions for sodium restriction in these trials was not limited to counselling, but included provision of food, prepared meals, or intensive inpatient training sessions.

**Methods/design:**

This is a parallel, randomized, controlled, open-label trial with blinded endpoints. Inclusion criteria are adult patients with hypertension with high dietary sodium intake (defined as ≥100 mmol/day). The control arm will receive usual care, and the intervention arm will receive usual care and an additional structured counselling session by a registered dietitian, with four follow-up telephone support sessions over four weeks. The two primary outcomes are change in sodium intake from baseline, as measured by a change in 24-hour urinary sodium measurements at four weeks and one year. Secondary outcomes include change in blood pressure (as measured by 24-hour ambulatory monitoring), change in 24-hour urinary potassium, and change in body weight at the same time points.

**Discussion:**

Though decreasing sodium intake has been reported to be efficacious in lowering blood pressure, there exists a gap in the evidence for an effective intervention that could be easily translated into clinical practice. If successful, our intervention would be suitable for outpatient programs such as hypertension clinics or interprofessional family practices (family health teams). A negative, or partially negative (positive effect at four weeks with attrition by 12 months) trial outcome also has significant implications for healthcare delivery and use of resources.

**Trial registration:**

The trial was registered with Clinicaltrials.gov (identifier: NCT02283697) on 2 November 2014.

**Electronic supplementary material:**

The online version of this article (doi:10.1186/s13063-015-0794-y) contains supplementary material, which is available to authorized users.

## Background

Hypertension is highly prevalent among adult Canadians (about 20 % in those aged 20 to 79 years), and is the most important modifiable risk factor for cardiovascular events, in particular stroke [1, 2]. The relationship between sodium intake as assessed from 24-hour urinary sodium and age-related increase in systolic blood pressure (BP) has been well established [3]. Furthermore, decreasing sodium intake has the potential to prevent or delay the development of hypertension and improve BP control, independently of BP lowering drugs, among hypertensive patients [4, 5]. With this in mind, it is not surprising that the restriction of dietary salt intake for the prevention and management of hypertension is a strongly endorsed health measure [6–8]. However, Health Canada survey findings indicate that the current average salt intake among Canadian adult males and females ranges between 6.5 and 9 g (or between 2,600 and 3,600 mg of sodium)/day, with men consuming more dietary salt than women [9]. However, according to the 2014 Canadian Hypertension Education Program (CHEP) guidelines, sodium intake should not exceed 2,000 mg/day [6]. Indeed, an individual would have to reduce their sodium intake by 50 to 70 %, depending on their hypertensive status, to reach the CHEP recommended target [6].

This magnitude of salt intake reduction to levels envisaged by the CHEP is projected to have a significant impact on BP level and on adverse vascular outcomes of hypertension [10]. It is estimated that 1.65 million deaths worldwide were due to cardiovascular causes from a daily sodium consumption of more than 2 g [11]. It is also estimated that the associated healthcare cost savings would amount to 10 to 24 billion US dollars annually [10]. Given the proven relationship between the dietary sodium intake and hypertension, the known risk of adverse outcomes of hypertension, and the individual and public health financial, health, and social benefits of low salt intake, it is somewhat surprising that salt intake remains stagnantly high over the last several decades, despite many public health efforts [9, 12].

Canadian adults are mostly diagnosed with high BP during routine annual check-ups with their family physician. Family physicians are expected to establish the diagnosis and to initiate hypertension therapy. Since the majority of hypertensive patients in Canada have mild and uncomplicated hypertension, primary care physicians also continue to manage a significant proportion of patients with hypertension [13]. Thus, with regards to the treatment of hypertension, family physicians are really the ‘front-liners’, who introduce both lifestyle modifications and pharmacological interventions to individual patients and make further adjustments in therapy to achieve target BP. The CHEP provides detailed guidelines on the diagnosis and treatment of hypertension to Canadian family physicians [6]. These guidelines include specific algorithms for the diagnosis and management of hypertension [6]. In the setting of very busy primary care practices, these algorithms are crucial to facilitate making the diagnosis, initiating and maintaining hypertension therapy, and ensuring that patients are engaged and informed.

However, in contrast to the specific algorithms provided for the diagnosis and pharmacological treatment of hypertension, algorithms on how to achieve the rigorous targets for dietary sodium intake are absent [6]. CHEP specifically endorses the Dietary Approaches to Stop Hypertension (DASH) diet [4] because it is well described, reproducible, and leads to sustainable decreases in salt intake. However, what is not clear from the guidelines is details about the most efficacious method of counselling on dietary sodium restriction to achieve potentially very rigorous targets, how to assess compliance and progress of an individual patient with regards to sodium intake restriction, and finally how to include these potentially time-consuming tasks into the daily routine of busy Canadian family physicians. Indeed, lack of time and inadequate compensations have been reported as the strongest barriers to providing nutrition guidance by US and Canadian primary practices [14–16]. These results should not come as surprise once one appreciates how much time primary care physicians in North America have ‘available’ for their patients. For example, results of the National Review of Medicine 2006 Practice Management Survey showed that majority of family physicians in Canada see 26 to 50 patients per day [17]. Further, 42 % of 700 responders reported an increase in patient load in the last 12 months [17]. A recent systematic review indicated that there are well-described, and therefore, easy to reproduce counselling methods on efficacious low sodium diets [18]. However, none of these counselling methods are suitable for hypertension management by primary care providers in Canada in the present form. The primary reason for the lack of feasibility in the outpatient settings in Canada is that interventions for salt restriction in these trials was not limited to mere counselling, but included provision of food, prepared meals, or intensive inpatient training sessions [18].

Hence, given that data from clinical trials support the efficacy of dietary sodium reduction in lowering BP, but with a paucity of research into clinically feasible and logistically simple methods of implementing this, we have designed a pragmatic clinical trial to test if the addition of lead counselling by a registered dietitian, in comparison to usual care, results in a change in dietary sodium intake.

## Methods/design

### Study design

The study is designed as a pragmatic, parallel, open-label, randomized controlled trial with blinded endpoints. Since the intervention is a counselling session, blinding will not be possible. However, the primary outcome of the study is a change in urinary sodium, which is an objective endpoint, and the laboratory personnel performing the measurement and the research personnel analyzing the measurements will be blinded to treatment assignment. The randomization process will consist of a computer-generated random listing of the treatment allocations in variable permuted blocks, with concealment of allocation using sealed envelopes. The Standard Protocol Items: Recommendations for Interventional Trials (SPIRIT) checklist and the World Health Organization (WHO) Trial Registration Data Set Checklist are also presented (see Additional file 1 and Table 1).

**Table 1 Tab1:** World Health Organization Trial Registration Data Set Checklist

Data category	Information
Primary registry and trial identifying number	ClinicalTrials.gov: NCT02283697
Date of registration in primary registry	4 November 2014
Secondary identifying numbers	-
Source(s) of monetary or material support	The Ottawa Hospital Academic Medical Organisation
Primary sponsor	The Ottawa Hospital Academic Medical Organisation
Secondary sponsor(s)	Ottawa Hospital Research Institute
Contact for public queries	[name] [name]
Contact for scientific queries	[name] PhD
	[name] MPH
Public title	Sodium counselling in hypertension
Scientific title	Does Pragmatically Structured Outpatient Dietary Counselling Reduce Sodium Intake in Hypertensive Patients?
Countries of recruitment	Canada
Health condition(s) or problem(s) studied	Hypertension
Intervention(s)	Active comparator: standard of care + Dietitian lead counselling
	Control comparator: standard of care
Key inclusion and exclusion criteria	Inclusion criteria:
	- adult patients (>18 years) with
	- hypertension defined as daytime blood pressure (BP) readings above 140/90 mmHg (as assessed from 24-hour ambulatory BP monitoring (ABPM)) without treatment
	- and/or any patient with treated hypertension irrespective of BP load based on 24-hour ABPM.
	Exclusion criteria:
	- Pregnant patients (since pregnancy and hypertension requires different dietary advice)
	Patients with following conditions:
	- eGFR <45 ml/min/1.75 m^2^,
	- active infection (defined as being on active anti-microbial treatment),
	- recent acute coronary syndrome (myocardial infarction or revascularisation) within 6 months,
	- psychiatric disorders and/or otherwise unable to sign consent,
	- patients with clinically manifested generalized and/or cardiac volume overload (including ascites and congestive heart failure) who may require immediate changes in diuretic therapy (at the discretion of treating hypertension specialist).
	- Inability to provide informed consent
Study type	Interventional
	Allocation: randomized
	Intervention model: parallel assignment
	Masking: blinding of outcomes assessor only
	Primary purpose: treatment
Date of first enrolment	June 2015 (anticipated)
Target sample size	120
Recruitment status	Funded, approved, enrolment to begin soon
Primary outcome(s)	Change in 24-hour urinary sodium from baseline at 4 weeks and 12 months
Key secondary outcomes	Changes in 24-hour urinary potassium, body weight, and BP

### Setting

The trial will be conducted at a tertiary care academic health sciences centre in Canada. The setting is a Renal Hypertension Clinic, which receives consultations for difficult-to-control hypertension. Potential participants will be identified from the clinic and approached by a member of the health care team to ascertain their willingness to be contacted by the research personnel. Once the patient has agreed to be contacted by the research personnel, a member of the research team will contact the patient and will briefly describe the trial and determine if the patient is interested in participating. If so, a copy of the consent form will be provided to the patient.

After reading the consent form, if the patient expresses interest, they will be asked to attend a screening visit where a study team member will explain the protocol, and potential risks and benefits again in detail. If the patient chooses to enroll in the study, the study coordinator will obtain written informed consent and ensure all necessary information is obtained. The research coordinator will ensure that, during the consent process, there is no overture of coercion, duress, or undue incentive.

### Study population

The inclusion criteria for this study are as follows:Adult patients (>18 years);Patients with hypertension defined as either daytime BP readings above 140/90 mmHg (as assessed from 24-hour ambulatory BP monitoring (ABPM)) without treatment, or any patient with treated hypertension irrespective of BP load; andDietary sodium intake >100 mmol/day, as measured with 24-hour urinary collection.

The exclusion criteria for this study are as follows:Pregnant patients (since pregnancy and hypertension requires different dietary advice);Patients with an estimated glomerular filtration rate (eGFR, measured using the MDRD formula [19]) <45 ml/min/1.75 m^2^;Patients with an active infection (defined as being on active anti-microbial treatment);Patients with recent acute coronary syndrome (myocardial infarction or revascularisation) within the last six months;Patients with psychiatric disorders and/or who are otherwise unable to sign consent; andPatients with clinically manifested generalized and/or cardiac volume overload (including ascites and congestive heart failure), who may require immediate changes in diuretic therapy (at the discretion of treating hypertension specialist).

### Interventions

Patients randomized to the control arm will receive a standard endorsement of low salt diet and other non-pharmacological interventions, such as moderation of alcohol intake, optimal body weight, and daily exercise, from a hypertension nurse and physician, which is the standard of care.

Patients randomized to the intervention arm will receive usual care and an additional one-on-one (family members allowed) one-hour long counselling session from a registered dietitian. The dietitian will assess the patient’s eating habits and identify factors involved in high sodium intake, focusing on portion size, processed food, snacking habits, eating out, and reading labels. Apart from counselling tailored to the cause and source of high sodium, a handbook with advice on decreasing sodium in diet will be provided. This will be followed by four weekly, 30-minute long follow-up sessions by telephone to provide support, address compliance, and answer any questions raised by patients and family members.

### Measurements

We will evaluate dietary sodium intake by measurement of 24-hour urinary sodium before and after counselling. We will not allow changes in diuretic therapy within a week prior to counselling and throughout the four weeks of the trial duration, and patients in whom an urgent change in diuretic therapy is anticipated will be excluded from the trial. This approach will ensure that baseline 24-hour urinary sodium reflects steady state and represents 24-hour dietary sodium intake. Similarly, changes in 24-hour urinary sodium four weeks post-intervention will reflect changes in patients’ dietary sodium intake with no interference of the effect of diuretics. In studies using the DASH diet and longer follow-up periods, the effect of intervention is attenuated once the food is not provided to the patient, and so does the effect on BP [20, 21]. Hence, we will have the sodium intake re-assessed 12 months post-intervention to assess for the long term effectiveness of this method.

24-hour ABPM will be done before and after dietary counselling within 24 to 48 hours of 24-hour urinary collection for sodium. This will allow us to correlate any changes in dietary sodium intake with changes in overall BP load. In addition, we will also measure changes in 24-hour urinary potassium, and changes in body weight. Lastly, a simple one-page survey will be administered to all patients to assess their perceptions of potential barriers to dietary sodium reduction at the end of the 12-month follow-up period. The time points of the intervention and data collection are shown in a schematic form in Fig. 1.

**Fig. 1 Fig1:**
[figure not shown]
Study flow diagram showing time points at which data will be collected. Figure legend: HT: Hypertension; MD: Medical Doctor, physician; RN: Registered Nurse; ABPM: Ambulatory Blood Pressure Monitoring

### Analysis

Though blinding of the patients is not possible for a behavioral intervention such as this, the assessment of the outcome, which is an objective measurement, will be done in a blinded fashion. All the study personnel collating and analyzing this data will be blinded to the treatment assignment. In addition, the laboratory personnel who will be measuring the urinary sodium (which is the primary outcome) will be blinded to treatment assignment.

We will have two primary efficacy outcomes, reduction in 24-hour urine sodium at four weeks and reduction in 24-hour urine sodium at 12 months. While we anticipate little or no loss to follow-up at four weeks, it is possible that there might be as much as a 30 % loss at 12 months. The minimal clinically important difference according to the CHEP guidelines is a 40 mmol reduction. Our review of the literature identified a range of possible standard deviations from 31 to 51 mmol. To be conservative, we assumed 51 mmol for the sample size estimation. Adjusting for multiple testing, this means that we would need 42 patients per group to have 90 % power in a t-test. In order to ensure this many patients at 12 months, we will recruit 60 patients per group. This calculation is conservative since it is based on a paired *t*-test but we will analyze the outcomes with the more powerful analysis of covariance (ANCOVA model.

Secondary outcomes will include changes in daytime average systolic BP by 24-hour ABPM, changes in dietary potassium intake assessed from 24-hour urinary potassium, and changes in body weight, all at the same time points as described for the primary outcome measure (four weeks as well as 12 months post-intervention). We will also do a one-page survey of participants at the end of the study (12 months) to identify potential barriers to salt restriction in diet.

All analysis will be conducted using the intention-to-treat principle. Any missing data will be imputed using multiple imputations. No interim analyses are planned, and there are no stopping rules for this trial. Subgroup analyses are planned based on tertiles of baseline sodium intake and source of high sodium intake (as identified by dietitian). We will also assess the association between changes in sodium, potassium intake, and changes in body weight and BP. In addition, we will conduct a sensitivity analysis based on achieved sodium intake and its relationship with BP. All the subgroup and sensitivity analyses will be hypothesis-generating and will be interpreted accordingly.

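### Effect modification by baseline sodium is planned only through tertiles; a continuous interaction with a non-linearity check would use the same data better (exploratory analysis, low severity)

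*Protocol article*

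**What the plan says.** In the Analysis section, the plan for baseline sodium as a modifier is one clause: "Subgroup analyses are planned based on tertiles of baseline sodium intake". A second subgroup factor, the source of high sodium, stands beside it. The section gives no cut-points, coding or interaction model, and no continuous analysis of baseline sodium as a modifier. It adds a general caveat: "All the subgroup and sensitivity analyses will be hypothesis-generating and will be interpreted accordingly".

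The same section fixes the setting. The primary outcomes are changes in 24-hour urinary sodium at four weeks and 12 months, and the model is ANCOVA ("but we will analyze the outcomes with the more powerful analysis of covariance"). The target is a 40 mmol difference ("The minimal clinically important difference according to the CHEP guidelines is a 40 mmol reduction"). The SD is taken from the top of a literature range of 31 to 51 mmol ("To be conservative, we assumed 51 mmol for the sample size estimation"). Sixty patients per group are recruited so that 42 remain if the 12-month loss reaches 30%; little or no loss is expected at four weeks. The Study population section makes a baseline 24-hour urinary sodium above 100 mmol/day an entry criterion, so every participant has the measurement.

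**The concern.** Tertiles are the article's stated choice for handling a continuous moderator, so this is not a detail left out. The choice has two consequences.

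First, if the counselling effect rises or falls steadily with starting intake, replacing intake by a three-level score throws away variation within each third and weakens the test for that trend.

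Second, the trial is sized for its main effect. A third of it is small: about 20 patients per arm, and about 14 observed per arm at 12 months under the planned maximum loss. Estimates within tertiles will be wide enough to differ noticeably by chance.

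What is at stake is the quality of an exploratory signal. The Discussion allows that a partially negative result might call for further help for some patients rather than all, so the question of who responds matters to the investigators' own reading. No primary or secondary conclusion rests on it.

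**Working it through.** **Inputs from the article (Analysis section).** 60 per group recruited, 42 per group after 30% loss, difference 40 mmol, SD 51 mmol (range 31 to 51), power 90%.

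**Assumptions.** Two-sided alpha 0.05 split over two primary outcomes, giving 0.025 (the alpha is not stated). The SD is used as the residual SD, with no gain from covariates. Imputation is taken to add no information beyond the observed patients. The shape of the baseline distribution is assumed, because the article gives none.

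**The plan's own figure.** A two-sample t-test with difference 40, SD 51 and alpha 0.025 has power 0.903 with 42 per group, and 42 is the smallest such number. Then 42 / 0.7 = 60. This reproduces "42 patients per group to have 90 % power in a t-test" and the recruitment target. The article also calls the calculation a paired t-test; the figure matches the two-sample form, which does not affect this point.

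**Size of a tertile.** 120 / 3 / 2 = 20 per arm at four weeks; 20 × 0.7 = 14 per arm at 12 months.

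**Precision within a tertile.** Half-width = t(0.975, 2n − 2) × SD × √(2/n).
- 12 months, SD 51: 2.056 × 51 × √(2/14) = 39.6 mmol.
- 12 months, SD 31: 2.056 × 31 × √(2/14) = 24.1 mmol.
- Four weeks, SD 51: 2.024 × 51 × √(2/20) = 32.6 mmol.

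The standard error of the difference between two tertile effects at 12 months is 51 × √(4/14) = 27.3 mmol (16.6 mmol at SD 31).

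**Information kept by a tertile score under a linear interaction.** This is the squared correlation between baseline and its score (−1, 0, 1). For a normal baseline it is (2φ(z₁/₃))² / (2/3) = (2 × 0.3636)² / 0.6667 = 0.793. The loss is 20.7%: 120 patients act like about 95, and 84 like about 67.

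| Assumed baseline shape | Loss |
|---|---|
| Uniform | 11% |
| Normal | 21% |
| Normal truncated at 100 mmol (means 140 to 180, SD 50 to 70) | 19% to 21% |
| Lognormal truncated at 100 mmol | 30% to 38% |

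A shifted exponential, a more extreme shape, gave 39%.

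**Cross-check.** With 42 per arm, the continuous slope has standard error 51 × √(2/42) = 11.1 mmol per baseline SD. The centres of the outer tertiles lie 2 × 1.09 = 2.18 SD apart, so that contrast has standard error 24.3 mmol, against 27.3 mmol from tertiles. (24.3 / 27.3)² = 0.79, as above.

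**Simulated power of the interaction test** (3,000 runs, SD 51, two-sided 0.05, normal baseline). Both the tertile trend and the 2-df test use tertile groups.

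| True pattern | Per arm | Continuous | Tertile trend | Tertile 2-df |
|---|---|---|---|---|
| Linear, 30 mmol per SD | 60 | 0.88 | 0.78 | 0.69 |
| Linear, 30 mmol per SD | 42 | 0.73 | 0.64 | 0.51 |
| Linear, 20 mmol per SD | 60 | 0.55 | 0.45 | 0.35 |
| Top third only, 45 mmol extra | 60 | 0.39 | 0.49 | 0.50 |
| Middle third only, 40 mmol extra | 60 | 0.05 | 0.05 | 0.40 |

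The interaction sizes are illustrative; the article gives none.

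**The case against.** The strongest reply is that the plan already limits what can be read from these analyses by calling them hypothesis-generating, and that nothing in the article is wrong or contradictory here. That stands, and it caps the severity. It does not make the less efficient analysis preferable, because an exploratory analysis is still worth doing well.

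A reader might infer that the continuous term is better at no cost. It needs no extra patients or data, but it assumes linearity. The last two rows of the power table show tertiles doing better when the effect sits only in the top or the middle third. Nothing in the article says which pattern to expect. This objection stands against a single linear term used alone, and it is why the fix includes a non-linearity check and keeps the tertiles.

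A reader might also infer that each tertile will be tested separately and judged on its own p-value, or that the cut-points will be sample tertiles. The article says neither; the test and coding may sit in an analysis plan that is not shown. Nor does it list the ANCOVA covariates, although a model for change in sodium would ordinarily include the baseline value.

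The ±40 mmol figure combines the maximum loss with the largest SD. Wide intervals also come mainly from the size of the trial. With 42 per arm and SD 51, the continuous model's half-width at the centre of an outer tertile is 1.99 × 11.1 × √(1 + 1.09²), or about 33 mmol. At 1.5 SD from the mean it is about 40 mmol. The change improves precision modestly; it does not make subgroup estimates precise.

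**Conclusion.** The point holds as a cheap improvement of low severity. Tertiles are the only stated route to effect modification by baseline sodium. For a roughly linear pattern they cost about 20% of the information if baseline is normal or truncated normal, and between 11% and 38% from the uniform to the most skewed truncated lognormal shape tried. These figures rest on assumed baseline distributions and on linearity. An unconditional loss of a fifth is more than the article supports, because it reports no mean, SD or shape for baseline sodium.

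Under the plan's most cautious inputs, a 12-month tertile estimate is uncertain by about as much as the 40 mmol difference the trial is built to detect; under milder inputs the interval is narrower. The sample size, the primary analysis and the trial's conduct are unaffected.

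**What to change.** Replace the tertile clause with wording such as: 'Effect modification by baseline 24-hour urinary sodium will be assessed by the arm-by-baseline interaction, with baseline as a continuous variable, in the ANCOVA for each primary outcome. Departure from linearity will be checked with a quadratic or spline term and its interaction with arm. The fitted effect and 95% confidence interval will be shown at set baseline values (for example 110, 150 and 200 mmol/day). Estimates with confidence intervals by tertile of baseline will be shown descriptively. These analyses are hypothesis-generating.' The baseline values are examples only and should be set before unblinding.

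The cost is a few words in the plan and one or two extra model terms, with no new data and no change in sample size. The downside is that the main test assumes linearity and can have less power than tertiles for a threshold or non-monotone pattern. The non-linearity check and the tertile display are there to bring such a pattern to notice.

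### On the text shown, the subgroup analysis by source of sodium cannot give a treatment effect by source, because only intervention patients see the dietitian who identifies it

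*Protocol article*

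**What the plan says.** The Analysis section of the protocol article plans two subgroup analyses, one by tertile of baseline sodium and one by "source of high sodium intake (as identified by dietitian". It classes all subgroup and sensitivity results as hypothesis-generating and applies multiple imputation to missing data without exception.

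The Interventions section describes what each arm receives.

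- **Control:** "Patients randomized to the control arm will receive a standard endorsement of low salt diet" and other lifestyle advice, "from a hypertension nurse and physician, which is the standard of care".
- **Intervention:** the same usual care plus a "one-hour long counselling session from a registered dietitian". In that session, "The dietitian will assess the patient’s eating habits and identify factors involved in high sodium intake", and the counselling is tailored to the result.

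Table 1 gives the same contrast: standard care with dietitian counselling against standard care alone. The Measurements section lists 24-hour urinary sodium and potassium, ambulatory blood pressure, body weight, and a one-page survey of perceived barriers at 12 months.

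**The concern.** A subgroup analysis in a randomised trial asks whether the treatment effect differs between kinds of patient. It needs the subgroup variable in both arms, so that treated and control patients can be compared within each category. Here the variable is defined by who records it, and that person's involvement is the randomised difference between the arms.

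At stake is one exploratory result. If the analysis is run as listed, it can only compare intervention patients who differ in their source of sodium. Such a difference may reflect how those patients would have changed anyway, and there would be no controls of the same kind to show it.

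**Working it through.** The point is structural, so the main check sets the sections side by side. The arithmetic only fixes the denominators and shows how small the cells would be under a repaired design.

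**1. Denominators (context only).** The inputs from the Analysis section are a difference of 40 mmol, an SD of 51 mmol, 90% power, an adjustment for multiple testing and 30% loss at 12 months. The adjusted alpha is not stated; I assume 0.05/2 = 0.025, two-sided.

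- Normal approximation: n = 2(2.2414 + 1.2816)² / (40/51)² = 24.82 / 0.6151 = 40.4, rounded up to 41 per group.
- Two-sample t-test: 41.6, rounded up to 42 per group, which is the article's figure.
- Recruitment: 42 / (1 − 0.30) = 60 per group, also the article's figure.

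**2. Where source is observed, on the text shown.**

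| Contact or measurement | Intervention (60) | Control (60) | Gives source of sodium? |
|---|---|---|---|
| Nurse and physician advice | yes | yes | none described |
| Dietitian session | yes | no | yes |
| 24-hour urinary sodium and potassium | yes | yes | no, amount only |
| Ambulatory blood pressure, weight | yes | yes | no |
| Barriers survey at 12 months | yes | yes | no; perceived barriers, at the end of follow-up |

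Source is therefore recorded for up to 60 of 60 intervention patients and 0 of 60 controls.

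**3. What can be estimated.** The effect in source category s is the mean outcome under intervention in s minus the mean outcome under control in s. The first term can be estimated. The second cannot, because no control is known to belong to s. The arm-by-source interaction is a difference between two such effects, so it cannot be estimated either.

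**4. Multiple imputation.** Imputing source for controls needs the relation between source and outcome under control, which no patient informs. A model that carries over the relation seen in the intervention arm fixes the interaction by assumption, and the data cannot check that assumption.

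**5. Cell sizes if source were recorded in both arms.** The Interventions section names five headings: portion size, processed food, snacking, eating out and label reading. Assume for illustration that each patient falls under exactly one, that the split is even, and that the SD is 51 mmol. With n patients per arm in a category, the standard error of the treatment effect is 51 × √(2/n). The standard error of the difference between two categories is √2 times that.

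| Time point | n per arm and category | SE of effect (mmol) | 95% half-width (mmol) | Half-width, difference between two categories (mmol) |
|---|---|---|---|---|
| 4 weeks | 60/5 = 12 | 20.8 | 1.96 × 20.8 = 41 | 1.96 × 29.4 = 58 |
| 12 months | 42/5 = 8.4 | 24.9 | 1.96 × 24.9 = 49 | 1.96 × 35.2 = 69 |

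Every half-width exceeds the 40 mmol difference for which the trial is sized. ANCOVA would narrow these intervals somewhat. Uneven or overlapping categories would make matters worse.

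**The case against.** **The full protocol may assess diet in everyone at baseline.** The article is a condensation, and Fig. 1 is not shown. An assessment of all patients before randomisation would remove the problem. This limit stands: the finding is about the text shown. That text is not silent, however. It names the variable, says who identifies it, and places that step in one arm.

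**A comparison within the intervention arm may be what was meant.** This is feasible, and the Analysis section promises no interaction test. But the item is listed as a subgroup analysis beside baseline sodium tertiles, which do exist in both arms, and nothing says it is confined to one arm.

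**The result is only hypothesis-generating.** This stands as a limit on impact. A reader might infer that the result is bound to be taken as effect modification; the article's own caution on interpretation does not support that. The caution does not, however, make the quantity estimable.

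**Stronger readings that the article does not support.**

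- *That the analysts' blinding is broken.* The article says "All the study personnel collating and analyzing this data will be blinded to the treatment assignment", and a source value held only for intervention patients would reveal the arm. But nothing says that the dietitian's classification enters the analysis file before the blinded work is finished.
- *That source is a product of treatment.* Eating habits exist before randomisation. Only their recording comes afterwards, and in one arm.
- *That regression to the mean will distort the result.* Patients are selected on high urinary sodium, so a raw before-after comparison would be exposed to it. But the article plans ANCOVA for the outcomes and does not specify a raw comparison here.

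**Conclusion.** The point holds. As described, the trial cannot deliver a treatment effect by source of sodium or an arm-by-source interaction, because source is recorded for up to 60 intervention patients and no controls. Only a non-randomised comparison within the intervention arm is possible.

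The consequence is small. One exploratory analysis is affected, while both primary outcomes, the sample size and the subgroup by baseline sodium tertile stand. The conclusion rests on two assumptions: that the full protocol adds no assessment of source for controls, and that subgroup analysis has its usual meaning of a treatment effect compared across subgroups.

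**What to change.** **Recommended.** Remove source of sodium from the subgroup analyses. Report it as a description within the intervention arm, and state that differences between sources give no evidence of effect modification. This costs one sentence and loses nothing that the described design could have delivered.

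**If a true subgroup analysis is wanted.** Record source in the same way in both arms before randomisation, for example with a short form at the screening visit, and test the arm-by-source interaction in the ANCOVA. The article reports that recruitment had not begun, and this works only for patients not yet randomised. It has real costs:

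- The questions cover the content of the counselling and may prompt controls to change, which would dilute the contrast.
- A self-reported variable replaces the dietitian's identification.
- A patient may fall under several headings, so a rule for a single category is needed.
- The cells would be small, about 12 per arm at four weeks and 8 at 12 months on an even split over five headings.

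**Precaution.** If the dietitian's classification is kept, hold it out of the analysis file until the blinded analyses are complete.
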